### Randomisation and blinding

Balanced randomisation [21] is used with random permuted blocks of 20 patients followed by a sequence of 11 blocks for 220 patients with a second, simple randomisation. Five digit random numbers from the RAND Corporation [22] are used for both steps. Based on this random list of digits an external co-worker, otherwise not involved in the trial, created 220 paper cards specifying the groups and inserted them in 1 to 220 serially numbered opaque, sealed envelopes. This stack of envelopes is kept in a locked safe at the QoL Unit at the Tumour Centre Regensburg and is accessible only by the two study coordinators.

Randomisation of individual patients is performed using the following described procedure. The study clinician in each of the four recruiting hospitals determines eligibility of the study patient. If all criteria are fulfilled and the patient has granted informed consent the study clinician sends the recruitment document to the QoL Unit. The study number 1 to 220 is determined by the exact date and time of fax entry. The CP will be informed by the QoL Unit about allocation of the individual patient either to the intervention or the control group.

The CP will be obliged not to share this knowledge with the patient. In order to control for bias, participants will be kept blind throughout the study about their allocated group (single blind design). At the end of the trial, the patients’ blindness about their allocated group will be checked.

At no point in the process will the recruiting clinician in the hospital access the sealed envelopes or be informed about the group allocation.

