#### Telephonic enquiries (CP)

Four weeks after the patient has filled out the QoL questionnaire, a member of the QoL Unit calls the CP by telephone and asks if anything has been done to improve the patient’s QoL. The reason for this is that in the intervention group CPs receive a QoL profile and an expert report with recommendations for improving their patients’ QoL. Therefore, whether anything has been done in response to the expert report is to be recorded by phone call. In order to ensure comparability of patients in both study arms, there are also telephonic enquiries for CPs of control group patients.

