#### Patient satisfaction (patient)

After the patient has finished the last QoL measurement at 18 months postoperatively, a questionnaire will be sent to the patient’s home. The questionnaire includes quantitative and qualitative questions on patient satisfaction regarding (medical) care since the diagnosis of colorectal cancer and usefulness of the repeated QoL measurements. Additionally, the blindness of patients about their allocated group is checked.

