### Ethics and monitoring

This study has received full ethical approval through the ethics committee of the University of Regensburg (internal reference number 12-101-0014). The trial is registered with ClinicalTrials.gov, trial registration number NCT02321813.

A central ethical question has to be answered before conducting a randomised trial: Is a new treatment denied to the control group from which those might benefit? In our study, control group patients are treated according to the S3-guideline for colorectal cancer (26) but do not receive additional targeted QoL therapy based on systematic diagnosis. Nevertheless, it can be expected that control group patients also benefit from study participation because their CP will also be trained in assessing QoL and therefore is expected to be sensitised for QoL deficits of his patient. It must also be considered that the new intervention or specific treatment of QoL might bear a risk for patients in the intervention group. Furthermore, emotional drain by filling out QoL questionnaires is conceivable. An insurance for patients’ safety was taken out to cover any possible harm of trial participants.

The randomised trial on breast cancer patients [6] did not show any evidence of possible harm elicited by the QoL pathway. For monitoring patient safety, patient’s CP is repeatedly contacted by phone about 1 month after the patient has filled out the QoL questionnaire (telephonic enquiries) and is asked whether he has recognised any negative effect on the patient. Serious adverse events, including death or admission to hospital, will be recorded, analysed, and reported to the local ethics committee.

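### Non-serious negative effects are described as coming only from the unblinded coordinating practitioner; no direct question to the blinded patient is described, so effects may be missed and any arm comparison is open to ascertainment bias

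*Protocol article*

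**What the plan says.** All references are to the protocol article.

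- **Possible harms (Ethics and monitoring).** Two are named. One is tied to the intervention: "the new intervention or specific treatment of QoL might bear a risk for patients in the intervention group". The other is tied to measurement: "emotional drain by filling out QoL questionnaires is conceivable".
- **How they are looked for (same section).** The CP is telephoned about one month after each questionnaire and "is asked whether he has recognised any negative effect on the patient". Serious adverse events, including death and hospital admission, are handled separately: recorded, analysed and reported to the ethics committee.
- **What the CP knows (Randomisation and blinding).** "The CP will be informed by the QoL Unit about allocation of the individual patient either to the intervention or the control group". The patient stays blinded throughout.
- **What the CP holds (Intervention group, Control group, Telephonic enquiries).** In the intervention arm he receives the QoL profile and an expert report with treatment recommendations. In the control arm he receives neither. Calls are made in both arms: "there are also telephonic enquiries for CPs of control group patients".
- **What the patient is asked (Procedure, Measures).** The EORTC QLQ-C30 and QLQ-CR29 before discharge and at 3, 6, 12 and 18 months. Then: "After the patient has finished the last QoL measurement at 18 months postoperatively, a questionnaire will be sent"; it covers satisfaction with care, usefulness of the repeated measurements and the blinding check.

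**The concern.** The article chooses a reporter for non-serious harm, and that reporter differs between the arms in what he knows. The intervention-arm CP knows the allocation, has the patient's scores in front of him, and is asked about harm from measures he may have arranged himself. The control-arm CP knows that his patient is a control and has no scores. He too must say only what he has recognised, about a month after the form.

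Emotional drain is felt by the patient and may never be mentioned to a doctor. The person best placed to report it is blinded and is already holding a form at each visit, yet no question on negative effects to that person is described.

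What is at stake is the safety statement, not the efficacy result. The article takes reassurance from the absence of evidence of harm in the earlier breast cancer trial, and it plans to extend the system to the whole of Germany. A similar statement from this trial would rest on unblinded third-party recognition. An analysis plan cannot repair that, because answers that were not collected cannot be analysed.

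**Working it through.** **1. Sources of harm information, side by side**

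| Source | Knows allocation? | Same information in both arms? | Asks about negative effects? |
|---|---|---|---|
| Telephone call to CP | Yes | No (profile and report in intervention arm only) | Yes |
| CP's written health status at 3, 6, 12, 18 months | Yes | No | Complications only |
| Patient EORTC forms, discharge to 18 months | No | Yes | No; they measure state |
| Patient questionnaire after month 18 | No | Yes | None stated |
| Serious adverse event record | Reporter not named | Not stated | Serious events only |

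The only row with an explicit question on negative effects below the serious threshold is the first. Its reporter is unblinded and informed differently by arm.

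**2. Which named harm bears on which problem**

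- Both arms fill out the same questionnaires at the same times, so drain from the questionnaires raises mainly a problem of missed cases.
- The risk attached to the intervention or QoL treatment is placed in one arm. The between-arm problem applies chiefly here.

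**3. Can the size be derived?**

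No. The article gives no rate of negative effects and no rate at which CPs recognise them, so there is no figure of the plan to reproduce. The only planned number used below is the enrolment of 110 per group.

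**4. Illustration (all rates are assumptions)**

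Let r be the true rate, equal in both arms, and s_I and s_C the shares recognised by the CP in the intervention and control arms.

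Observed rate = r × s. Observed ratio = (r × s_I)/(r × s_C) = s_I/s_C, whatever r is. Share missed = 1 − s.

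| r | s_I | s_C | Observed, intervention | Observed, control | Ratio |
|---|---|---|---|---|---|
| 20% | 50% | 50% | 10% | 10% | 1.00 |
| 20% | 40% | 60% | 8% | 12% | 0.67 |
| 20% | 30% | 70% | 6% | 14% | 0.43 |
| 20% | 60% | 40% | 12% | 8% | 1.50 |
| 10% | 60% | 30% | 6% | 3% | 2.00 |

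In patients, the last row is 110 × 10% = 11 truly affected per arm, of whom 11 × 0.60 = 6.6 and 11 × 0.30 = 3.3 would be reported.

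The absolute difference scales with r. For 40% against 60% recognition it is 2 points at r = 10% (4% against 6%) and 6 points at r = 30% (12% against 18%).

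**5. Reading of the illustration**

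The first row is under-counted but comparable. The other rows show a false deficit or a false excess in the intervention arm. Direction follows entirely from which recognition rate is assumed to be higher, and both orders are plausible: a CP holding the profile may notice more, and a CP who arranged the measure may report less.

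**The case against.** The strongest case on the other side has five parts.

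- **No comparison is planned.** The call is introduced as safety monitoring. Neither the outcomes section nor the statistical section lists a comparison of non-serious effects between arms. *This stands.* The point concerns what may later be said from these data, not a pre-specified test.
- **Blinded patient data already exist.** Thirteen self-reported scales, including emotion, pain and fatigue, are collected in both arms, and randomisation allows net worsening to be attributed to the arm. *Largely right for average effects.* But the scales do not ask whether a form or a measure did harm. A measure that helps most patients and harms a few would disappear in the group scores. Drain from questionnaires that both arms complete would not appear as a difference at all.
- **Calls are made in both arms, and control CPs also receive the outreach visit.** *True.* This equalises the schedule and the general awareness, but not knowledge of allocation or access to the profile.
- **An article condenses the full protocol.** A patient item may exist there. *Possible.* If so, citing it closes the point. The concern rests on the reporter the article does state, not on an omitted detail.
- **A loosely worded patient item would mostly collect effects of cancer treatment.** The article itself notes that adjuvant therapy and stoma reversal are often unfinished at 6 months. *This stands*, and the item has to be narrowed accordingly.

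A reader might go further and infer that harm is under-counted, that the arms are not comparable, or that the patient is never asked anything relevant. The documents do not support this. They give no rates from which under-counting could be derived; equal recognition would leave the arms comparable; and patients do report their state repeatedly. What can be said is that no explicit question on negative effects to the patient is described.

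**Conclusion.** The point holds in limited form. As described, non-serious negative effects reach the trial through an unblinded CP who is informed differently in the two arms, although a blinded patient is available to answer. Such effects may be missed, and a between-arm statement or a conclusion of no harm would be open to ascertainment bias.

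Neither size nor direction can be derived. The ratios of 0.43 to 2.00 under equal true rates rest on assumed recognition between 30% and 70% and show only that differences in recognition alone can create or hide an imbalance.

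Serious adverse events are not affected: they are recorded and analysed separately, and death and admission are largely objective. The primary endpoints, their tests and the sample size are untouched. The conclusion assumes that no fuller document already contains a patient item. It is a worthwhile, inexpensive improvement to safety monitoring, not a threat to the main result.

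**What to change.** - **Add one identical item with free text** to the patient form in both arms at 3, 6, 12 and 18 months. It should ask whether filling out the questionnaire, or any measure started to improve quality of life since the last form (as distinct from cancer treatment), had a negative effect. Word it so that it does not reveal allocation.
- **Use the patient's answer as the main source** for any descriptive between-arm report of non-serious negative effects.
- **Keep the CP's telephone answer as a supplement**, labelled as unblinded.
- **Report how many patients were asked at each visit, by arm**, because recruitment began in January 2014 and some visits will precede the change.

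**Cost:** a slightly longer form, a short amendment and more reports to review. Visits already completed will have no item data, so the early follow-up of the first patients cannot be recovered. No extra staff are needed, and no endpoint or sample size changes.

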### Primary and secondary outcomes

The first primary endpoint (1) will be the proportion of patients in both groups with diseased QoL (<50 points in at least one dimension) 12 months postoperatively. Twelve months were chosen because adjuvant therapies and stoma reversal are often not finished 6 months postoperatively.

The second primary endpoints (2), enhancing the credibility of the first primary endpoint, are the rates of patients with diseased QoL in each dimension of the profile 12 months after surgery.

The primary endpoints formulated above will be tested in the strict order (1), (2), that is, a statistical testing procedure with a priori ordered hypotheses is applied [31]. This binary primary endpoint was chosen for two reasons: (1) according to our conceptual groundwork [5, 19] 50 score points on a 0 to 100 QoL scale defines healthy versus diseased QoL, and (2) the same primary endpoint was used in our randomised trial on breast cancer patients and generated a significant difference according to our hypothesis [6].

### Sample size

The trial sample size was calculated by means of the first primary endpoint (lack of a QoL deficit in the QoL profile, that is, all scores are ≥ 50 score points). Based on the randomised controlled trial on breast cancer patients (6), we expect that 45 % of the patients in the intervention group report no QoL deficit 12 months after therapy, but only 25 % in the control group. Setting α at 5 % and power (1-β) at 80 %, 89 patients are needed in each group in order to detect the hypothesised difference when calculating the *Χ*^2^ test. To compensate for 20 % drop-outs (death or refusal) within the 12 months observation period, we will enrol 110 patients per group, and thus, the total sample size will be 220.

### Statistical analyses

Trial data are entered into a Microsoft ACCESS (version 2007) database, which is installed on a password-protected computer without physical connection to the internet. All data entered into the database are controlled by a second, independent member of the QoL Unit.

All variables will be presented using descriptive statistics (frequencies, percentages, means/standard deviations, medians/interquartile ranges, and various graphical representations). Point estimates will be accompanied by confidence intervals.

The design for the two primary endpoints is based on a method of fixed a priori ordered hypotheses [31]. Thus, the second primary endpoints will only be analysed, if the null hypothesis of the first primary endpoint can be rejected (*P* < 0.05). This design assures a global alpha of 0.05. The analyses of the primary endpoints (including both first and second primary endpoints) will be conducted using the *Χ*^2^ test (or Fisher’s exact test if the smallest expected cell value is < 5), setting the level of statistical significance at *P* < 0.05. It is not planned to use imputation to handle missing data in primary analysis.

Statistical tests regarding the secondary endpoints will also use the *P* < 0.05 significance threshold, but all secondary results will be interpreted in an exploratory manner.

Secondary analyses will start with an ANCOVA using the continuous QoL data as dependent variable and baseline QoL, comorbidity, sex, age and study site as covariates. Other secondary analyses will focus on exploratory subgroup analyses. These include the influence of different surgical procedures on QoL and the benefit these different subgroups gain from the QoL pathway. Furthermore, risk factors for diseased QoL (ASA, stoma, type of tumour (colon/rectum), age and sex) will be investigated. Tests of significance will include the Mann-Whitney *U* test, Kruskal Wallis test, *t*-test, and ANOVA or McNemar, depending on the number of groups, their independence/dependence, and the scaling of the dependent variable.

For qualitative data in the final questionnaire about patient satisfaction, a category system will be created and answers will be categorised by independent raters, so that frequencies of key categories can be quantitatively analysed by using descriptive statistics [32].

A detailed statistical analysis plan (SAP) will be written before all analyses commence.

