### Measures

#### Quality of life (patient)

Quality of life is measured by using the validated QoL questionnaire of the European Organisation for Research and Treatment of Cancer (EORTC), consisting of a core module (EORTC QLQ-C30 [25, 28]) and a module for colorectal cancer patients (EORTC QLQ-CR29 [23, 24]). The questionnaire is a self-administration instrument with a multidimensional structure measuring QoL on a four-point Likert scale or rather on a seven-point Likert scale for the global dimension QoL. Satisfying internal consistency and good retest-reliability, as well as construct and clinical validity, have been demonstrated [24, 28, 29].

In every dimension scores are uniformly transferred to a scale from 0 (very bad QoL) to 100 (very good QoL). A cut-off score has been constructed, which defines scores < 50 points as diseased QoL. This score has been extensively discussed and accepted in the present form by consensus of a large group of clinicians [5, 6, 18].

For outcome measurement of the present randomised trial, 13 different scales have been selected according to the results of the previous randomised trial in breast cancer patients [6], the appraisal of relevance for QoL of colorectal cancer patients, and the availability of therapy options (global QoL, physical functioning, role functioning, pain, discomfort during defecation, increased bowel movement, discomfort during urination, body image, emotion, concentration/remembering, fatigue, family life/social encounters, and financial situation).

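### The gate protects the step from endpoint (1) to endpoint (2), but not the 13 unadjusted dimension tests inside step (2), so the stated global alpha of 0.05 is not assured

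*Protocol article*

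**What the plan says.** The section on primary and secondary outcomes defines the first primary endpoint as a score below 50 in at least one dimension at 12 months. The second primary endpoints "are the rates of patients with diseased QoL in each dimension of the profile 12 months after surgery". The section on quality of life measurement gives their number: "13 different scales have been selected". The description of the QoL profile agrees, since it counts global QoL plus 12 dimensions.

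The only order given is (1) before (2). The statistical analyses section sets the gate: "the second primary endpoints will only be analysed, if the null hypothesis of the first primary endpoint can be rejected" at P < 0.05. It follows with "This design assures a global alpha of 0.05". One test rule then covers everything called primary: "The analyses of the primary endpoints (including both first and second primary endpoints) will be conducted using the" chi-square test (Fisher's exact test for small expected counts), "setting the level of statistical significance at *P* < 0.05".

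No order among the dimensions, no adjustment, and no rule that all must be significant is stated. The exploratory label is reserved for the secondary endpoints.

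**The concern.** In a fixed-sequence design, a step may hold several hypotheses only if that step is itself tested with a procedure that controls its own error. Here step (2) is 13 parallel tests, each at the full 0.05. The gate protects all of them when there is no effect anywhere. If the pathway helps on some dimensions, the gate is meant to open, and each unaffected dimension then has its own 5% chance of a false claim.

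What is at stake is the statement of which deficits the pathway improves. Those results carry the label primary and are covered by an explicit error guarantee, so readers could take a single significant dimension as confirmed.

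**Working it through.** **Inputs from the protocol article.** No-deficit rates at 12 months are 45% vs 25%, so composite deficit rates are 55% vs 75%. There are 89 evaluable patients per group, alpha is 0.05, power is 80%, and 13 dimensions are each tested at 0.05.

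**Inputs assumed, because the article gives neither.** These are the correlation between dimensions (exchangeable, 0.3 to 0.5) and the number of dimensions truly affected.

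**1. Reproduce the sample size.** With pooled rate 0.35:

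n = [1.96·√(2·0.35·0.65) + 0.8416·√(0.45·0.55 + 0.25·0.75)]² / 0.20² = (1.322 + 0.555)² / 0.04 ≈ 88.1, so 89.

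This matches the article. Power at 89 per group is 0.804.

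**2. Reproduce the stated alpha.** If no dimension is affected, simulation of the gated procedure opens the gate in about 5% of trials. The gate opens and at least one dimension is also falsely significant in about 3%. The stated 0.05 holds in this case.

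**3. Approximate the error when endpoint (1) truly differs.** With k unaffected dimensions, treat the tests as independent of each other and of the gate:

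P(at least one false dimension claim) ≈ 0.804 × (1 − 0.95^k)

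**4. Compare with simulation.** The simulation used 89 per arm, 75% vs 55% composite deficit and correlation 0.3 to 0.5.

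| Dimensions affected | k | 1 − 0.95^k | × 0.804 | Simulated |
|---|---|---|---|---|
| 3 | 10 | 0.401 | 0.32 | 0.27-0.31 |
| 6 | 7 | 0.302 | 0.24 | 0.21-0.22 |
| 9 | 4 | 0.185 | 0.15 | about 0.13 |
| 11 | 2 | 0.098 | 0.08 | 0.06-0.08 |
| 12 | 1 | 0.050 | 0.04 | 0.03-0.04 |
| 13 | 0 | 0 | 0 | 0 |

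The hand calculation and the simulation agree closely. Simulation error and the choice of baseline rates move the 3-to-6 rows by a point or more, so roughly 20-31% is the fair statement for them.

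**5. Condition on the first two rows.** If all 13 dimensions had the same control deficit rate, an effect in only 3 or 6 of them could not produce the planned composite drop. Those rows need affected dimensions with higher baseline rates than the rest. At correlation 0.3, for example, with 3 affected, these fall from about 35% to 9% while the others stay at 10%. With 6 affected, these fall from about 23% to 5% while the others stay at 13%. The rows for 9 to 12 affected dimensions use equal control rates.

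**6. With Holm inside step (2).** In the same kind of scenario the error is at most about 3.5%. The first threshold is 0.05/13 = 0.0038.

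**The case against.** **The effect may be broad.** The scales were chosen partly because therapies exist for them, so each is a treatment target. With 12 or 13 dimensions affected, the error stays below 5%. This stands, and it is why the size must be given as a range. But the article asserts the guarantee without condition, and no passage limits it to a broad effect.

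**Global alpha may mean error under the global null only.** On that reading the sentence would be correct. It fits poorly with a method of ordered hypotheses in which every member is labelled primary, because such ordering is meant to protect later steps when earlier ones are truly false.

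**The dimension tests are supportive, and an SAP is to follow.** They are indeed described as adding credibility to endpoint (1), and no passage announces a confirmatory claim for a single dimension. But they are called primary and placed under the guarantee. The article does not leave the matter open: it fixes the test, the threshold and the conclusion. An SAP that added an adjustment would have to depart from this text.

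**Stronger readings that the documents do not support.** A reader might infer an error of 1 − 0.95^13 = 49%. That figure needs all 13 dimensions to be unaffected, in which case the composite is normally unaffected too and the gate caps the error near 5%. A reader might also infer that a several-hypothesis step is invalid in itself. It is not; what is missing is a rule within the step.

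**Conclusion.** The sentence is wrong as written. The procedure holds 0.05 if no dimension is affected, but not in much of the range the trial is powered for. Under the planned composite rates with 89 per arm, the chance of at least one false dimension claim is roughly 20-31% with 3 to 6 affected dimensions, about 13% with 9, 6-8% with 11, and below 5% with 12 or 13. These figures rest on an assumed exchangeable correlation of 0.3 to 0.5 and, for 3 to 6 affected dimensions, on higher baseline deficit rates in those dimensions.

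A reader might infer that the trial's main conclusion is compromised. It is not: the test of endpoint (1) keeps its 5% level and the sample size calculation stands. The point should be fixed because a false guarantee is attached to endpoints labelled primary, but it is not critical to the trial.

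**What to change.** Keep the gate, and choose one of the following for step (2):

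- Test the 13 dimensions with Holm (or Hochberg) at a family level of 0.05.
- Prespecify a complete order of all 13, each at 0.05, stopping at the first non-significant result.
- Label the dimension comparisons descriptive and limit the global-alpha sentence to endpoint (1).

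Reword the sentence in the statistical analyses section to match the choice, before any analysis.

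The change is to wording only. The cost of Holm is lower power for single dimensions, since the smallest P value must be at most 0.05/13 = 0.0038. The cost of a fixed order is that dimensions late in the list may never be reached. The cost of the descriptive label is that no dimension result is confirmatory. Endpoint (1), enrolment and trial conduct do not change.

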### Procedure

Written informed consent is obtained from each participant before they are included into the study. All participants (intervention and control group) repeatedly fill out a QoL questionnaire (EORTC QLQ-C30, QLQ-CR29 [23–25]) at the following times: 0 to 2 days before discharge from hospital and 3, 6, 12 and 18 months postoperatively. The first QoL measurement takes place in hospital and the further measurements (3, 6, 12, 18 months postoperatively) are carried out in the CP’s practice during follow-up. For each assessment time point participants receive a postal reminder. Guideline for colorectal cancer [26] recommends first follow-up at 6 months. Colorectal cancer patients suffer a lot of QoL deficits especially in the first months of treatment. Therefore, we decided also to measure QoL 3 months postoperatively. Feasibility of this additional measurement is expected to be good because most patients visit their CP regularly. This could be also observed in the pilot phase of the study.

Parallel to the QoL measurements, the patient’s CP provides additional information about the patient’s health status. All data are sent to the QoL Unit at the Tumour Centre Regensburg.

All patients are treated according to the follow-up regimen of S3-guideline for colorectal cancer [26]. Concomitant care is not prohibited but will be collected and considered in secondary data analysis.

Differences between the treatment of intervention group and control group patients is shown in the following section. Figure 2 gives an overview of the study flow in the two arms of the randomised trial.

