#### Health status (surgeon/CP)

The first measurement of health status is performed before discharge from the hospital. The surgeon gives information about the following demographic and medical characteristics of the patient: age, sex, marital status, children, occupation, ASA classification, tumour stage, date of surgery, surgical procedure, complications, comorbidities, (neo)adjuvant therapies, other current or planned therapies (for example, pain therapy, psychotherapy physiotherapy), CEA, preoperative symptoms, height, and weight. The type of surgery and ASA classification especially are expected to affect strongly colorectal cancer patients’ QoL [30]. These variables will be considered in data analysis, but neither specific surgical procedures nor higher ASA classifications will be excluded in order to achieve high external validity.

During follow-up the CP gives written information about health status at 3, 6, 12 and 18 months postoperatively regarding CEA, finished, current, or planned therapies, and complications. Additionally, the CP makes an assessment of the patient’s global QoL on a seven-point Likert scale.

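### The primary chi-square test is valid but leaves unused the baseline QoL, type of surgery and ASA data; adjusting for them could add 0 to about 10 points of power

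*Protocol article*

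**What the plan says.** Statistical analyses, on the test: "The analyses of the primary endpoints (including both first and second primary endpoints) will be conducted using the" chi-square test, with Fisher's exact test if the smallest expected cell count is below 5. No covariates are named and no imputation is planned. The first primary endpoint (Primary and secondary outcomes) is the "proportion of patients in both groups with diseased QoL (<50 points in at least one dimension) 12 months postoperatively". The second primary endpoints, the deficit rates in each dimension, are tested only if the first is significant.

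On the data available:

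- Procedure: all participants complete the questionnaire "0 to 2 days before discharge from hospital and 3, 6, 12 and 18 months postoperatively", so a baseline on the outcome instrument exists by design.
- Health status (surgeon/CP): "The type of surgery and ASA classification especially are expected to affect strongly colorectal cancer" patients' QoL. Both factors are recorded before discharge.
- Participants and recruitment: eligibility is not restricted by surgical procedure or ASA score, and the analysis is to take both into account.
- Randomisation and blinding: balanced randomisation "is used with random permuted blocks of 20 patients", as one list of 220 numbers assigned in order of fax arrival. No stratification is described.

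Adjustment for baseline appears in one place, a secondary ANCOVA of continuous QoL. Its covariates are baseline QoL, comorbidity, sex, age and study site. Surgical procedure and ASA are not among them; they enter only exploratory subgroup and risk-factor analyses.

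**The concern.** The protocol admits patients broadly on two factors that it regards as strongly prognostic, does not describe balancing them by design, and says they will be taken into account. Yet the comparison on which the conclusion rests uses neither of them, nor the baseline value of the outcome instrument. The one adjusted treatment comparison is exploratory, concerns continuous scores rather than the binary endpoint, and omits surgery and ASA.

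What is at stake is precision. If these variables predict the 12-month endpoint, an adjusted analysis detects the same effect with higher probability and no extra patients. A reserve would be useful here. The planning effect is carried over from a breast cancer trial, and the control group's practitioners also receive the outreach visit, which Ethics and monitoring expects to sensitise them to QoL deficits. Because testing is ordered, a miss on the first endpoint also closes every dimension test.

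**Working it through.** **Inputs from the document (Sample size section).**

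- Anticipated deficit-free rates: 0.45 (intervention) and 0.25 (control).
- Test settings and stated result: "Setting α at 5 % and power (1-β) at 80 %, 89 patients are needed in each group".
- Loss of 20 %, with 110 randomised to either arm.

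Sidedness is not stated; two-sided is taken because it reproduces the stated figure.

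**Step 1: reproduce the stated figure.** Pooled, uncorrected formula with mean rate 0.35:

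n = [1.96·√(2·0.35·0.65) + 0.8416·√(0.45·0.55 + 0.25·0.75)]² / 0.20² = (1.3221 + 0.5551)² / 0.04 = 88.1, rounded up to **89 per group**. This matches exactly. A continuity correction would give 98, and a one-sided test 70.

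**Step 2: power of the planned test after drop-out.** 110 × 0.8 = 88 analysable per arm.

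Power = Φ[(0.20·√88 − 1.3221) / 0.6596] = Φ(0.840) = **79.96 %**. At 89 per arm it is 80.4 %.

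**Step 3: power with adjustment.** Let R² be the share of the variance of the binary endpoint explained by the covariates. The documents give no value; 0 to 0.25 is an **assumption**. The variance of the adjusted risk difference shrinks by about (1 − R²), so the effective size is 88/(1 − R²), put into the Step 2 formula. The last column is 89·(1 − R²), rounded up.

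| Assumed R² | Effective n per arm | Power | Gain (points) | n per arm for about 80 % |
|---|---|---|---|---|
| 0 | 88.0 | 80 % | 0 | 89 |
| 0.05 | 92.6 | 82 % | 2 | 85 |
| 0.10 | 97.8 | 84 % | 4 | 81 |
| 0.15 | 103.5 | 86 % | 6 | 76 |
| 0.20 | 110.0 | 88 % | 8 | 72 |
| 0.25 | 117.3 | 90 % | 10 | 67 |

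**Step 4: check by simulation.** 4000 trials per setting, 88 per arm, 45 % vs 25 %, one standard normal baseline covariate, chi-square test against the Wald test of the arm coefficient in an adjusted logistic model:

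| R² | Chi-square | Adjusted |
|---|---|---|
| 0 | 81.1 % | 80.8 % |
| 0.04 | 79.7 % | 81.7 % |
| 0.10 | 80.4 % | 83.9 % |
| 0.135 | 79.6 % | 85.8 % |
| 0.23 | 80.6 % | 89.9 % |

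Type I error was 4.6 % to 5.7 % for both tests. The simulation standard error of each power figure is about √(0.8·0.2/4000) = 0.6 points, so the two routes agree.

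**Step 5: which baseline measure.** A second simulation (2000 trials per setting, same rates) took assumed latent baseline-to-12-month correlations of 0.3, 0.4, 0.5 and 0.6.

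- Continuous baseline score: adjusted power 84, 84, 87 and 89 %.
- Binary baseline deficit status, 90 % prevalence at discharge (assumed): 82, 81, 82 and 84 %, against 79 to 82 % unadjusted.
- The same at 95 % prevalence (assumed): 81, 81, 83 and 82 %, against 80 to 81 % unadjusted.

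A prevalence that high is plausible but not documented. The Background says deficits peak in the first months after surgery, and 100 − 25 = 75 % of controls are still expected to have one at 12 months. A yes/no baseline deficit would then recover little of the gain.

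**The case against.** The strongest reply is that nothing in the primary analysis is wrong. Under randomisation the chi-square test is valid, it tests the difference in proportions the trial was sized on, its sample size reproduces exactly, and the endpoint follows the earlier breast cancer trial. It also needs no covariate data, whereas a model could lose patients with a missing baseline value unless a rule is added. All of this stands.

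A reader might infer more than the documents support:

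- *That the trial is underpowered or gives up power for nothing.* The planned test meets its 80 % target to within rounding, and the size of any loss cannot be derived from the document; at R² = 0 it is zero.
- *That the lack of stratification biases the primary result.* A factor present in 30 % of patients (assumption) has an imbalance SD of √(2·0.3·0.7/110) = 0.062, so a 12-point difference arises in about 5 % of trials. That is ordinary random variation, already covered by the test's type I error.
- *That the undertaking to take surgery and ASA into account is broken.* Both appear in exploratory analyses. They are absent only from the primary test and the ANCOVA.

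It can also be said that adjustment is partly planned and that a detailed SAP is promised. But the ANCOVA does not address the binary endpoint, and the primary test is fixed in the protocol, so an SAP that follows it would inherit the choice.

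**Conclusion.** The point holds as an efficiency improvement that should be made, not as an error in the plan. The primary test is valid and consistent with the sample size, but has no power reserve at 88 per arm (79.96 %) and does not use prognostic data the trial already collects. Adjustment would add between 0 and about 10 points of power over an assumed R² of 0 to 0.25, with type I error unchanged. The gain rests wholly on that undocumented association, and on using a baseline measure that still discriminates between patients at discharge.

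**What to change.** Before any analysis, pre-specify the following in the SAP and align the protocol's statistical section with it.

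- **First primary endpoint:** logistic regression on arm with a small covariate set: a continuous or count baseline QoL measure (for example mean profile score, or number of dimensions below 50, but not binary deficit status), type of surgery/stoma, ASA and hospital.
- **Reporting and decision:** give the standardised (marginal) risk difference with 95 % CI, which keeps the 20-point planning scale, and name one test as decisive, for example the test of that risk difference.
- **Missing covariates:** a simple stated rule that keeps every patient with a 12-month outcome in the analysis.
- **Supportive analysis:** the chi-square test as now planned.
- **Second primary endpoints:** adjust each dimension for its own baseline score, with a pre-stated fallback to the chi-square or Fisher test where deficits are too rare to fit the model.

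The cost is wording and slightly more modelling, plus the rules for missing covariates and non-convergence. No new data or patients are needed.
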